## Interventions

### Explanation for the choice of comparators {6b}

The control arm participants will receive an enhanced usual care, while the intervention arm participants will receive both an enhanced usual care and a collaborative care psychosocial intervention. The main component of the intervention is a psychosocial programme delivered at home by trained CHWs who have additional support through weekly supervision and an application installed on tablet computers.

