### Intervention description {11a}

#### Enhanced usual care

This comprises improved recognition of depression by the research team (screening with the PHQ-9 to identify depression) followed by usual care. The research team will send a list with the names of the individuals included in the study to UBS managers (in the control and intervention arms). The research team will not interfere with usual care—for instance, prescription of medications, CHW usual monthly home visits or access to family doctors or mental health specialists.

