#### Instruments

The three main instruments used in this study are the PHQ-9 (at the screening and follow-up assessments), the EQ-5D-5L and the ICECAP-O.

The PHQ-9 [30, 44] is a well-validated brief depression measure extensively used in clinical research, including Brazil [45], among other reasons because it is sensitive to changes over time [44, 46]. Acute suicide risk will be assessed with a standardised questionnaire whenever the ninth question of the PHQ-9 is scored 1 or more.

The EQ-5D [34, 47] is a generic preference-based outcome measure that provides a common metric for policy-makers to compare the cost-effectiveness of treatment in diverse clinical settings. The EQ-5D is sensitive to changes in mental health outcomes in the literature [48, 49], and the new five-level version was correlated with changes in the PHQ-9 scores in the pilot study [22].

The ICECAP-O [35] measure will be used to assess broader wellbeing/capability (for example, independence, security) of participants. We have registered the intention to use both EQ-5D and ICECAP-O instruments with the developers of these instruments.

We will also collect information on participants’ sociodemographic profile, health condition, anxiety symptoms (GAD-7) [37], social network (Lubben Social Network Scale-6—LSNS-6 [50, 51]), stressful life events [38], smoking habits, alcohol use (Alcohol Use Disorders Identification Test-Consumption—AUDIT-C) [52], disability, behaviour activation (BADS-SF) [36], loneliness (3-item University of California, Los Angeles (UCLA) loneliness scale) [53], work loss productivity, use of private care, need of care, use of medication for chronic conditions, consultations with healthcare professionals and admission to hospital. The economic assessment will also include resources used during the CHW training and supervisory sessions and data collected from medical records and the public health system databases (consultations and procedures).

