### Adverse event reporting and harms {22}

In this study, serious adverse event (SAE) data will be collected—that is, any untoward medical occurrence that is believed by the investigators to be causally related to study intervention. SAEs can result in any of the following: death, attempted suicide, life-threatening situations (that is, immediate risk of death) or significant physical or emotional disability/incapacity. SAEs of individuals who discontinued participation will not be reported. CHWs and sub-contracted RAs will be trained to obtain SAE information from visits. The intervention coordinator will be responsible for the completion of SAE forms and contacting the principal investigator, when necessary. Where appropriate, reports should be forwarded promptly to the Ethics Committee of the USP Medical School, with a copy to the DMC chair. A SOP for SAE recording, management and reporting was also developed to guide the team.

We do not think that this trial poses any considerable risks to trial participants. The intervention to be evaluated adds to existing usual care, and the trial does not prevent family doctors or other FHT professionals initiating or changing treatment for depression or any other health problem. None of the components to be tested is considered harmful.

The risk of suicide among depressed participants will be assessed regularly, and participants at high risk at any stage will receive immediate support from the sub-contracted RA or CHW, something that does not occur at present. CHWs and sub-contracted RAs will be trained in assessing risk with a standardised protocol, and CHWs will also receive ongoing supervision of their cases. A safety plan has been developed to deal with these emergencies and tested during our pilot study with two participants at risk of suicide while receiving the pilot psychosocial intervention. The safety plan was applied successfully by the CHWs in the pilot study. As part of this safety plan, these participants were seen by the family doctor for further assessment and subsequently managed by the FHT.

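### Serious adverse events are defined by believed causation, so the SAE data cannot support an unbiased comparison of harms between arms

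*Protocol article*

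**What the plan says.** The harms section {22} states that SAE data will be collected and explains the term as "any untoward medical occurrence that is believed by the investigators to be causally related to study intervention". The next sentence reads "SAEs can result in any of the following: death, attempted suicide, life-threatening situations" and goes on to serious disability or incapacity. These outcomes are listed as possible results of an SAE, not as what makes an event one.

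The section adds that SAEs in people who have discontinued are not reported. Community health workers (CHWs) and the sub-contracted research assistants are trained to pick up SAE information at visits. On paperwork it says "The intervention coordinator will be responsible for the completion of SAE forms", with reports forwarded where appropriate to the ethics committee and copied to the DMC chair. On risk it says "The intervention to be evaluated adds to existing usual care" and "None of the components to be tested is considered harmful". It refers to an SOP for SAEs, which is not reproduced.

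The section on the choice of comparators {6b} says "The control arm participants will receive an enhanced usual care", while the intervention arm receives that and the psychosocial programme. The description of enhanced usual care reads: "This comprises improved recognition of depression by the research team (screening with the PHQ-9 to identify depression) followed by usual care".

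**The concern.** Seriousness is a property of what happened. Relatedness is a judgement about why it happened. A comparison of harms between randomised arms needs the first, collected in the same way in both arms. The second can then be examined as a subset. The article's definition merges the two and lets the judgement decide whether an event is counted.

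The judgement also cannot work alike in the two arms, because the thing to which events must be attributed is given in only one. Within that arm, inclusion depends on an opinion about a programme whose components the same section declares not to be harmful.

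Participants are aged 60 or over and depressed, so deaths and suicide attempts are the harms a reader will look for. The article reports that the pilot's safety plan was used for two participants at risk of suicide while receiving the programme. If such events are filtered by attribution, neither an excess nor a reassuring balance between arms can be read from the SAE data.

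**Working it through.** No arithmetic applies. The article gives no event rate and plans no calculation on SAEs, so the check consists of setting the statements side by side.

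1. **Entry condition.** The only criterion stated for an SAE is "any untoward medical occurrence that is believed by the investigators to be causally related to study intervention". The sentence on outcomes says what SAEs can result in and adds no second route. An event with one of those outcomes but without the belief in causation falls outside the definition.

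2. **What the causal belief must attach to.** The article does not define the study intervention. The harms section itself uses the word for something that is extra: "The intervention to be evaluated adds to existing usual care". The comparators section gives that extra element to one arm only.

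3. **Control arm.** From steps 1 and 2, an event in a control participant would have to be believed caused by a programme that the person did not receive. On this reading control participants can have essentially no SAE, whatever happens to them.

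4. **Intervention arm.** A death or suicide attempt that the investigators attribute to illness, age or circumstance does not meet the definition. It is not recorded as an SAE and does not enter the route that runs through the SAE form to the principal investigator, the ethics committee and the DMC chair.

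5. **Would equal ascertainment repair it?** No. If every event in both arms were found with the same effort, the definition would still drop the unattributed ones and, in effect, those of the control arm.

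6. **Does other text repair it?** The section on instruments collects "consultations with healthcare professionals and admission to hospital", but as participant information and not as safety data. Acute suicide risk is assessed when the ninth PHQ-9 item is positive. This serves the care of the individual and is not described as a count by arm. The section on auditing {23} sends recruitment and retention checks by arm to the DMC, so deaths could show there as losses. No text available for this review provides for recording serious events regardless of attribution, or for tabulating them by arm.

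7. **A second restriction.** Leaving out SAEs after discontinuation narrows the data further. It would also contradict a definition that runs to the 12-month follow-up, so the two have to be settled together.

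**The case against.** **The article is a condensed account.** The SAE SOP is not shown and may use a wider definition. This limits what can be said about practice. It does not excuse the wording, because the article states a definition outright and does not leave it open. If the SOP is wider, the two documents conflict; if it agrees, the flaw is in operation.

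**Study intervention could be read more broadly.** Enhanced usual care stands under the heading of intervention description {11a} and includes screening by the research team. The research assistants who carry out assessments in both arms are trained to obtain SAE information, which suggests that collection in both arms was intended. This stands in part. A reader might infer that the control count is exactly zero by construction, but the article does not go that far, since an event blamed on screening is conceivable. The broader reading would still leave out every unattributed death or suicide attempt in both arms.

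**Serious events may be visible elsewhere.** This also stands in part. A reader might infer that unattributed deaths are never counted anywhere, or can never reach the DMC. The documents do not support that. Deaths may appear as attrition, retention by arm goes to the DMC, and admissions are collected. Part of the oversight section was not available for this review, so the DMC's full remit cannot be judged. The supportable claim is narrower: such events are not counted as SAEs and do not enter the SAE route described.

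**The judgement may not lie with unblinded or interested staff.** The definition names the investigators. The intervention coordinator completes the forms, and the article does not say that the coordinator decides causation. The point therefore does not rest on who judges.

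**Randomisation, primary outcome, analysis and power are untouched.** This is true. The defect concerns safety monitoring and the reporting of harms.

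**Conclusion.** The definition is wrong as written. It makes believed causation the condition for being an SAE, which leaves the control arm with essentially no SAEs on the natural reading and removes unattributed serious events from the intervention arm. The SAE data cannot then support an unbiased comparison of harms in either direction.

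The conclusion rests on taking the article's definition at its word and, for the statement about controls only, on reading the study intervention as the added psychosocial programme. It needs no assumed event rate. Any figure for missed events or for a spurious difference would require rates of events and of attribution that the documents do not give, so none is offered.

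It does not follow that the trial is unable to learn anything about harms. Attrition and admission data exist, but they are collected for other purposes and do not replace a count of serious events by arm.

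**What to change.** - **Definition.** An SAE is any untoward medical occurrence in a participant of either arm, from consent to the 12-month follow-up, that results in one of the outcomes already listed in the harms section, whether or not it is thought related to the intervention.
- **Relatedness.** Record it as a separate field on the form.
- **Reporting.** Give the DMC and the final report all SAEs by allocated arm, with related SAEs as a subset.
- **Discontinuation.** Reconcile the sentence that leaves out people who discontinued, so that those who stop the intervention but have not withdrawn consent to the use of their data are still counted. The consent section {26b} already asks participants about data use after withdrawal.
- **SOP.** Align it with the new wording, or, if it is already wider, correct the article's description to match.

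The change alters no treatment and no part of the primary analysis. It costs a revised definition, form and SOP and an amendment. The downside is more events to log in an older population. Recruitment had begun before this protocol version, so serious events among participants already enrolled would have to be collected retrospectively as far as records allow.

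### The article's list of serious outcomes omits hospital admission, so an admission involving none of the listed outcomes is not an SAE, and no safety use is stated for the admissions the trial collects

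*Protocol article*

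**What the plan says.** Under *Adverse event reporting and harms {22}*, an SAE is "any untoward medical occurrence that is believed by the investigators to be causally related to study intervention". The section then says what such an event may lead to: "SAEs can result in any of the following: death, attempted suicide, life-threatening situations (that is, immediate risk of death", followed by "or significant physical or emotional disability/incapacity". That makes four outcomes, and hospital admission is not one of them. The section does not describe any collection of non-serious adverse events.

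Two further statements in the section matter here. One narrows what is reported: "SAEs of individuals who discontinued participation will not be reported". The other points to a separate operating procedure: "A SOP for SAE recording, management and reporting was also developed to guide the team".

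Hospital admission is mentioned only under *Instruments*, where a long list of participant information ends with "consultations with healthcare professionals and admission to hospital". The next sentence begins: "The economic assessment will also include resources used during the CHW training and supervisory sessions and data collected from medical records". The word 'also' implies that the preceding items feed the economic assessment, though the text does not say so outright. Nothing in the available text sends admissions to SAE review, to the DMC or to a safety table.

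**The concern.** Participants are 60 or older and score at least 10 on the PHQ-9. The programme is delivered at home by lay health workers, with escalation decided by the Family Health Team. In that setting an admission, and a psychiatric one in particular, is a plausible sign that someone got worse. If it involved no death, suicide attempt, immediate danger to life or significant incapacity, the stated definition does not make it an SAE. No other safety route for it is described.

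At stake is what the trial can say about harm. The harms section states that none of the components tested is thought harmful. A safety record that may leave out admissions tests that statement less well than it could, although admissions are being collected anyway.

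**Working it through.** The plan gives no figure on this point, so the check is a reading of the definition against kinds of admission. The inputs are the four listed outcomes, the causality condition and the exclusion after discontinuation (all from the harms section), and the collection of admissions (from *Instruments*).

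| Kind of admission | SAE as the article stands | SAE if admission is added to the list | In an all-cause table by arm |
|---|---|---|---|
| With a suicide attempt, judged related to the intervention | Yes | Yes | Yes |
| With immediate danger to life or significant incapacity, judged related | Yes | Yes | Yes |
| With none of the four outcomes, judged related | **No** | Yes | Yes |
| Any admission judged unrelated | No | **No** | Yes |
| After the person has discontinued participation | Not reported | **Not reported** | Only if admissions are still recorded for that person |

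Three things follow.

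1. The omission itself affects the third row only.
2. Adding admission to the list repairs that row and leaves the fourth and fifth as they are, because the causality condition and the discontinuation rule still apply. The causality condition is the larger restriction. Control participants do not receive the psychosocial programme, so few or none of their admissions could be attributed to it. SAE counts would not give a fair comparison between arms even with a longer list.
3. A table of all-cause admissions by arm needs no causality judgement and so covers the first four rows.

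On size, the documents contain no admission rate. Purely as an assumption, if 5% to 15% of participants had at least one admission in 12 months, the totals would be 1440 × 0.05 = 72 and 1440 × 0.15 = 216. These are all-cause totals over both arms. They show roughly what the table by arm might hold under that assumption, before attrition. They do not measure the third row: they include unrelated admissions, and admissions that already meet a listed outcome. For the third row they are no more than an upper bound, conditional on the assumed rates.

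**The case against.** The case on the other side has real force on several points.

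- **How much is lost.** A reader might infer that every admission short of immediate danger to life stays out of the safety record. The text does not support that. A suicide attempt and significant incapacity each qualify without such danger. The incapacity may be emotional and need not be lasting, so an admission for marked worsening of depression could well meet it.
- **Use of the admission data.** A reader might also infer that admissions are held solely as a cost item and never looked at for safety. The economic use is implied and exclusive use is not stated. All that can be said is that no safety use is given.
- **Timing.** It is tempting to assume that admissions are asked at both the 8- and 12-month interviews. The economic analyses compare arms over 12 months and also estimate cost per recovery at 8 months, which makes this likely. But *Instruments* gives no timing for the item, and the schedule in Fig. 1 is not shown.
- **Other signals.** Worsening is also watched through the PHQ-9 at every home session, regular assessment of suicide risk with a safety plan, and comparison of PHQ-9 between arms at 8 and 12 months. Admission is not the only signal of harm.
- **The unseen procedure.** An operating procedure covers SAE recording and reporting, and it may count admissions. So it cannot be established that no form would ever be completed for one. Part of the oversight section was also not available.

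The last point does not remove the concern. The article does not leave seriousness to the procedure: it states the list itself, with nothing to mark it as a set of examples. If the procedure counts admissions, the published list is incomplete and the two need reconciling. If it does not, the gap is real.

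**Conclusion.** The concern holds in a limited form. Under the article's definition, an admission involving none of the four listed outcomes is not an SAE, and the article states no safety use for the admissions it collects. This is a fault in a stated rule, not detail left to another document.

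The number of events affected cannot be given. It depends on an admission rate that the documents do not supply, on how many admissions would be judged related, and on how 'significant' incapacity is applied. Nor do the documents support saying that the safety conclusion would rest on too few events. The small effect of the list alone is itself informative: while the causality wording stands, the comparison of admissions between arms is what would add most.

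The primary analysis is untouched. The point should be acted on because the improvement is cheap. It rests on two assumptions: that the published list is the one in force, and that admissions are asked in the same way in both arms.

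**What to change.** 1. Produce a table of all-cause hospital admissions by arm, with psychiatric admissions shown separately, from the data already collected. Supply it to the DMC and include it in the trial report, whatever the judged causality. This is the main remedy.
2. Add admission to hospital to the list of outcomes in the harms section. If the SAE procedure already counts it, bring the published list into line instead.
3. Confirm at which visits admissions are asked, that both arms are asked in the same way, and whether the answers allow psychiatric admissions to be identified.
4. State in the report that SAE counts cover only events judged related to the intervention and leave out people who discontinued participation, so that readers do not take them as a full comparison between arms.

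The cost is a short edit to the definition and the procedure, some additional SAE forms and one extra table, which is a modest reporting burden. If forms for planned or clearly unrelated admissions are a worry, those can appear in the table only. *Trial status* records a pause in recruitment and foresees possible amendments, so there is a practical occasion for the change.

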### Frequency and plans for auditing trial conduct {23}

We will audit the recruitment (and retention) rates across arms to investigate the extent of any differential recruitment/retention and if any bias might accrue in terms of depression scores. The DMC will be informed of the findings of these checks.

### Plans for communicating important protocol amendments to relevant parties (e.g. trial participants, ethical committees) {25}

Any modifications on the study design, recruitment, study procedures, intervention, data collection and data analysis agreed between the research team, TSC and DMC will be communicated to the Ethical Committees and funders. Guarulhos health system managers will also be notified and need to agree with any modification related to the daily functioning of their health units. Protocol amendments will only be implemented after appropriate approval has been received.

## Dissemination plans {31a}

We expect to publish the results in internationally competitive journals, something in which we have a good track record [18, 19, 21, 55–57]. We will present the project and results at local, regional and international conferences in any of the relevant disciplinary fields. Additional dissemination will be through the Centre for Global Mental Health websites and programme of extramural activities. We will engage King’s College London’s press office and public engagement coordinator. There will be media engagements and other dissemination activities. Dissemination in Brazil will be assisted by the press officers of the institutions involved. The core group of investigators will convene 1 month before the end of the study to discuss results and plans. In parallel, we will organise dissemination meetings and workshops with main stakeholders to discuss results and potential impact of scaling up. We will arrange meetings of our experts with our main stakeholders to assist us in the process of enlisting their support and persuading them of the importance of this and other similar future projects. We have an intensive plan of dissemination of the results involving policy-makers as well as potential funders/donors in this field.

